### Sample size

Since no similar article was found on breastfeeding in mothers with gestational diabetes, first a pilot study will be conducted to determine the sample size.

### Data analysis

After collecting quantitative data, the data will be analyzed by SPSS software 21. The normality of data distribution of quantitative variables will be evaluated using the Kolmogorov–Smirnov test. Independent t-test/Mann–Whitney will be used to compare normal/abnormal quantitative variables in two groups (inter-group) and paired t-test/Wilcoxon will be used to compare normal/abnormal quantitative variables (intra-group). A significance level of 0.05 will be considered.

**Quantitative program evaluation** In a quantitative study, the impact of the educational program for mothers with gestational diabetes will be evaluated using the “breastfeeding Drop” survey tool, which is planned based on the planned theoretical constructs. With this tool, changes in “attitude, subjective norms, perceived behavior control, intention, and behavior” will be measured and compared in two intervention and control groups.

**Tool description** The “Breastfeeding Drop” survey tool, is a valid and reliable 52-question Likert-scale tool based on the theory of planned behavior and has the domains of “attitude, subjective norm and perceived behavioral control about breastfeeding”, and was designed by Janaki in 1994. This tool is also known as the “Breastfeeding Behavior Assessment Tool”. Out of 52 items of this tool, 29 are attitudinal items, 13 items are related to subjective norms and 10 items are related to perceived behavioral control. Participants will answer each item of this questionnaire on a six-point rating scale. Based on the theory of planned behavior, attitude items as beliefs related to the consequences of a certain behavior are multiplied by the score resulting from its positive or negative evaluation [29]. The validity and reliability of this tool were done in Iran in 2015 [30].

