The results obtained in the previous phases will reveal which structures (attitude, subjective norms, perceived behavioral control, intention, and behavior) have the highest priority as the focus of intervention planning. In addition to the results of the qualitative part of the study, the results of the pre-test will show which structures have the highest and lowest scores, which structures have the most problems, and which structures are more important for learning. Based on the results obtained from the qualitative stage and the results of the pre-test, the researcher will explore, and review interventions and programs of changes regard to breastfeeding behavior in Iran and other countries and search in reliable scientific databases. After that, to determine the educational content and plan educational sessions in the field of breastfeeding behavior of these mothers, a meeting will be held consisting of the research team and a group of health, gynecology, and pediatric experts from the health department of Mashhad and Ardabil University of Medical Sciences. By using the existing instructions and guidelines and the opinions of the research team and experts, the appropriate educational methods are selected to achieve the set goals according to the structures of the theory of planned behavior. To achieve each goal, the best and most applicable educational method must be determined. Based on this, at the end of this stage, the design and implementation of the plan will be determined. Then, the (educational) content will be provided to a group of mothers with gestational diabetes to ensure its comprehensibility.

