### Quantitative phase methodology

Quantitative studies are regular and systematic studies in which data are collected objectively and phenomena are studied with precise and quantitative measurements. In these studies, the obtained data are tested or described with statistical techniques [23]. Interventional studies are a type of quantitative method used to test scientific hypotheses. In experimental methods (randomized controlled clinical trials and semi-experimental designs) an intervention program is used to achieve the goals of the test, which is measured through a set of predetermined indicators. In semi-experimental designs, there is a comparison group that has the same basic characteristics as the intervention group, and after the implementation of the intervention program in the intervention group, any difference between the results of the control and intervention groups is measured [27]. Semi-experimental designs facilitate the investigation of causality in situations where complete control is not possible. Pre-test-post-test design with a comparison control group is the most common design used in research [28]. In the current mixed study, the quantitative phase will aim to determine the impact of education based on the theory of planned behavior on the breastfeeding behavior of women with gestational diabetes, which includes implementation and evaluation.

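### The between-arm test is picked by a normality check and is not baseline-adjusted, and the text leaves open whether post scores or changes are compared

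*Protocol article*

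**What the plan says.** All statements below are in the protocol article.

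- **Gate.** In the quantitative Data analysis section: "The normality of data distribution of quantitative variables will be evaluated using the Kolmogorov–Smirnov test. Independent t-test/Mann–Whitney will be used to compare" the groups.
- **Between arms.** In full, the second of these sentences begins: "Independent t-test/Mann–Whitney will be used to compare normal/abnormal quantitative variables in two groups (inter-group"). No covariate and no model is named.
- **Within arms.** "paired t-test/Wilcoxon will be used to compare normal/abnormal quantitative variables (intra-group"). This uses the pre-test.
- **Level.** "A significance level of 0.05 will be considered".
- **Quantity compared.** The program evaluation paragraph of the same section says that changes in the five constructs of the theory "will be measured and compared in two intervention and control groups".
- **Pre-test.** The third-phase objectives list before/after comparisons of behaviour and of intention. The section on elaborating the intervention adds that "the results of the pre-test will show which structures have the highest and lowest scores". The methodology section remarks that "Pre-test-post-test design with a comparison control group is the most common design used in research".
- **Allocation.** The sampling section assigns two health centres to each arm and takes the controls from the other centres. The sample size is left to a pilot study.

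**The concern.** There are three linked weaknesses.

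1. **The data choose the test.** A t-test addresses a difference in means and Mann–Whitney a shift in ranks. Letting a Kolmogorov–Smirnov result decide means that what is estimated is settled only after the data are seen, and may differ from one construct to the next. The check has little power in small samples and rejects trivial departures in large ones, so it is a poor guide at either end.
2. **No baseline adjustment between arms.** The pre-intervention scores enter the within-arm tests, but those do not compare the arms. Neither named between-arm test can condition on the baseline score. Precision is lost, and any measured baseline difference between the arms passes into the result. With four centres, allocation cannot be relied on to balance baseline.
3. **The compared quantity is not fixed.** The text can be read as comparing post scores or as comparing changes. These have different variances and react differently to a baseline difference.

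**Working it through.** The article gives no sample size, effect size, SD, pre–post correlation or intracluster correlation (ICC), so there is no figure of its own to reproduce. The values of r (pre–post correlation), ICC, mothers per centre (m) and the 0.5 SD effect below are assumptions.

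**Step 1: precision, mothers treated as independent, equal pre and post SDs.** Relative variance of the arm difference:

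- post-only: 1
- change score: 2(1 − r)
- ANCOVA: 1 − r²
- ANCOVA relative to change score: (1 − r²) / [2(1 − r)] = (1 + r)/2

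| r | Change | ANCOVA | ANCOVA / post-only | ANCOVA / change |
|---|---|---|---|---|
| 0.3 | 1.40 | 0.91 | 0.91 | 0.65 |
| 0.5 | 1.00 | 0.75 | 0.75 | 0.75 |
| 0.7 | 0.60 | 0.51 | 0.51 | 0.85 |

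The inverse ratio minus 1 gives the extra mothers that the less efficient analysis would need:

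- Against post-only: 1/0.91 − 1 = 10%, 1/0.75 − 1 = 33%, 1/0.51 − 1 = 96%.
- Against change scores: 1/0.65 − 1 = 54%, 1/0.75 − 1 = 33%, 1/0.85 − 1 = 18%.

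Illustrative numbers per arm for 0.5 SD, two-sided 0.05, 80% power, no clustering, at r = 0.3 / 0.5 / 0.7:

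- post-only: 63
- change: 88 / 63 / 38
- ANCOVA: 58 / 48 / 33

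**Step 2: chance baseline imbalance with two centres per arm.** In SD units, the SD of the baseline difference between arms is √[ICC + (1 − ICC)/m]. With ICC 0.05 and m = 25: √(0.05 + 0.95/25) = √0.088 = 0.297. If the same r holds at centre level, a post-only comparison carries r × 0.297 of this: 0.15 SD at r = 0.5 and 0.21 SD at r = 0.7. These two figures apply to the post-only reading alone.

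**Step 3: what adjustment leaves behind.** If a stable difference of s SD between the arms' centres persists fully to follow-up, ANCOVA on mothers leaves about (1 − r)s of it: 0.7s, 0.5s and 0.3s at r = 0.3, 0.5 and 0.7.

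**Step 4: type I error with two centres per arm.** Simulation under no effect, 2,000 runs per setting, nominal 5%, range over r = 0.3 to 0.7:

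| m | ICC | Post-only t-test | ANCOVA on mothers |
|---|---|---|---|
| 20 | 0.01 | 7–8% | 7–8% |
| 20 | 0.05 | 16–17% | 15–18% |
| 20 | 0.10 | 25–26% | 25–26% |
| 40 | 0.01 | 8–10% | 9–10% |
| 40 | 0.05 | 24–28% | 26–27% |
| 40 | 0.10 | 37–39% | 38% |

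A t-test on the four centre means stays near 5% (4% to 6% across settings). It has 4 − 2 = 2 degrees of freedom, so its critical value is 4.30 rather than 1.96. Adjusting for baseline on individual mothers therefore does nothing for the clustering error.

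**The case against.** **The pre-test is used.** A reader might infer that it is collected and then ignored. The documents do not support that: the paired tests use it, pre-test scores guide programme design, and the mention of changes compared in the two groups can naturally mean a between-arm change score. What stands is narrower. The between-arm test is not baseline-adjusted, and the text does not settle which quantity it compares. On the change-score reading the 96% at r = 0.7 falls to 18% and the 0.15–0.21 SD carry-over does not apply, but ANCOVA is still the more precise analysis at every r below 1.

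**The evidence for a baseline is uneven.** The methodology remark on pre-test–post-test designs is general, and the pre-test that guides programme design need not come from trial participants. The before/after objectives, the paired tests and the word changes are the firmer support. Breastfeeding behaviour is a real exception: the quantitative inclusion criteria admit women who are still pregnant, for whom a behaviour score before birth may mean little.

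**Covariates usually belong in an analysis plan.** That is true, and silence would be no finding. But this article is not silent. It names the between-arm tests, neither of which takes a covariate, and it names the gate that chooses between them.

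**Centre allocation is the larger problem.** This also stands. A chance imbalance between randomly allocated centres is extra variance rather than bias, and adjustment on individual mothers leaves the standard error wrong.

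**Conclusion.** The point holds in limited form. The article lets a normality test on the trial's own data choose the between-arm test, does not adjust that comparison for baseline although pre-intervention scores are measured, and does not fix whether post scores or changes are compared.

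The precision gain depends on the assumed correlation and on treating mothers as independent. For r between 0.3 and 0.7, the ANCOVA variance is 0.91 to 0.51 of post-only and 0.65 to 0.85 of change-score. No size is attached to the normality gate; that part rests on reasoning.

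A reader might go further and infer that ANCOVA would remove baseline imbalance at no cost. The documents do not support this. With two centres compared with two others, adjustment reduces the measured imbalance only. Centre-level and unmeasured differences remain, and the type I error on individual mothers stays at about 7% to 38% for ICC 0.01 to 0.10 and 20 to 40 mothers per centre.

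**What to change.** In the quantitative Data analysis section:

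1. Remove the Kolmogorov–Smirnov gate.
2. For each construct with a meaningful pre-test, prespecify one between-arm estimate: the post-intervention score adjusted for the baseline score of the same construct, reported as an adjusted mean difference with a 95% CI. This also settles the choice between post scores and changes.
3. Keep a rank-based or bootstrap analysis as sensitivity only.
4. Place this estimate inside an analysis that respects centre, through a random centre effect or centre-level summaries of baseline-adjusted scores, with about 2 degrees of freedom. Do not enter centre as a fixed effect: each centre belongs to one arm, so it is collinear with arm and the arm effect could not be estimated.
5. Say which constructs have a usable baseline. If behaviour has none in women still pregnant, adjust the other constructs only.

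**Cost.** Baseline adjustment is a free improvement: it needs wording only, since the plan already measures the pre-intervention scores, and the pilot can supply r for the sample size. Item 4 is not free, because the move from a critical value of 1.96 to 4.30 is a real loss of power. It follows from the allocation by centre and is needed with or without baseline adjustment.

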**Methods/design:**

A mixed methods exploratory design will be used to conduct this study in 3 phases. The first phase (qualitative): The purpose of the first phase is to understand the experience of breastfeeding mothers who had gestational diabetes, which will be done using the directed content analysis method. The purposive sampling will be used on pregnant mothers with gestational diabetes 30–34 weeks and mothers with infants (up to 6 months) with a history of gestational diabetes. The second phase include designing and implementing an educational program based on the PBT: Education will be conducted based on the needs assessment of the qualitative phase, the opinions of the focus group, and the literature review, then the breastfeeding behavior will be measured using the survey tool of “breastfeeding drop”. The third phase: Interventional quantitative phase: The sample size will be carried out by a pilot study, then a designed program as an educational intervention for teaching breastfeeding behavior based on the PBT for 30–34 weeks pregnant mothers with gestational diabetes will be implemented during 3–4 sessions and breastfeeding behavior will be evaluated after delivery.

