### Specific objectives of the qualitative stage

Explanation of breastfeeding behavior of women with gestational diabetesExplaining the perceived behavioral beliefs of women with gestational diabetes about breastfeeding behaviorExplaining the perceived subjective norms of women with gestational diabetes about breastfeeding behaviorExplanation of perceived control beliefs of women with gestational diabetes from breastfeeding behaviorExplaining the behavioral intention of women with gestational diabetes regarding breastfeeding

The general goal of the second quantitative stage: designing an educational program based on the theory of planned behavior.

Specific Objectives of the second phase of educational program design:Assessment and prioritization of the educational needs of women with gestational diabetesDetermining the goals and activities of the educational program for women with gestational diabetes.Evaluation design of educational program designed for women with gestational diabetes

The overall goal of the third quantitative phase: determine the effect of the implementation of the educational program based on the theory of planned behavior on the breastfeeding behavior of women with gestational diabetes.

The specific objectives of the third phase are to determine the effectiveness of the implementation of the educational program: which will be measured based on the “breastfeeding drop prediction tool”.Determining the comparison of breastfeeding behavior of women with gestational diabetes before and after the implementation of the interventionDetermining the comparison of breastfeeding intention of women with gestational diabetes before and after the implementation of the intervention

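### As described, the Breastfeeding Drop tool has no item for intention or behaviour, the two outcomes the third phase sets out to compare

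*Protocol article*

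**What the plan says.** The third-phase goal appears in the list under the heading Specific objectives of the qualitative stage. It is to "determine the effect of the implementation of the educational program based on the theory of planned behavior on the breastfeeding behavior of women with gestational" (the quote stops one word short of the condition's full name). Two comparisons follow, each before versus after the intervention: breastfeeding behaviour and breastfeeding intention. Effectiveness is something "which will be measured based on the “breastfeeding drop prediction tool". The Abstract (Methods/design) agrees: "the breastfeeding behavior will be measured using the survey tool of “breastfeeding drop". It adds that behaviour will be assessed after delivery, without naming another measure or a time.

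In the quantitative Data analysis section, the paragraph on programme evaluation states: "With this tool, changes in “attitude, subjective norms, perceived behavior control, intention, and behavior” will be measured and compared in two intervention and control groups". The tool description that follows says that the instrument "is a valid and reliable 52-question Likert-scale tool based on the theory of planned behavior". It gives the domains as "attitude, subjective norm and perceived behavioral control about breastfeeding" and divides the items: "29 are attitudinal items, 13 items are related to subjective norms and 10 items are related to perceived behavioral control". It also gives the tool a second name that contains the word behaviour.

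**The concern.** Two adjacent paragraphs disagree on what the instrument measures. One lists five constructs. The other lists three and assigns every item to them. The two constructs left over are the two that the third phase names for comparison.

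At stake is what a positive result would mean. The programme is built on the theory's constructs, so it teaches towards attitude, norms and control. A higher score afterwards would show that beliefs moved towards what was taught. Reported under the stated objectives, the same result would be read as an effect on breastfeeding behaviour although no feeding had been recorded. In the theory as the Background presents it, perceived control and intention make a behaviour likely; they are not the behaviour. Analysis cannot recover an outcome that was not collected.

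**Working it through.** **Item count.** All inputs come from the tool description in the quantitative Data analysis section.

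- Stated total: 52 items.
- Attitude 29, subjective norms 13, perceived behavioural control 10.
- Sum: 29 + 13 + 10 = 52, which reproduces the stated total.
- Items left for intention or behaviour: 52 − 52 = 0.
- Shares: 29/52 = 55.8%, 13/52 = 25.0%, 10/52 = 19.2%.

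**Constructs claimed against constructs covered.**

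| Construct | Claimed for the tool | Items described | Third-phase comparison |
|---|---|---|---|
| Attitude | yes | 29 | no |
| Subjective norms | yes | 13 | no |
| Perceived control | yes | 10 | no |
| Intention | yes | 0 | yes |
| Behaviour | yes | 0 | yes |

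The tool as described covers 3 of the 5 constructs, and neither of the two named for comparison.

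**Is another measure named?** No. The article gives no feeding record, no definition of behaviour (exclusive, any, stopped) and no intention scale. The post-delivery assessment in the Abstract has no instrument of its own.

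**Can behaviour be compared before and after?** The Abstract places the programme at 30–34 weeks of pregnancy. A mother at that stage is not yet feeding this infant, so there is no baseline feeding behaviour to compare with. A belief questionnaire can be given then; a feeding measure cannot. For mothers enrolled in pregnancy, behaviour can only be compared between groups after delivery.

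**Which infant age is possible?** The quantitative inclusion criteria admit pregnant mothers beyond 36 weeks and mothers with infants in the first 6 months. The cohort cited in the Background assessed stopping at 1, 3, 6 and 12 months. For an infant enrolled close to 6 months, ages 1 and 3 months have passed, and 6 months would fall before 3–4 sessions were finished. Of those four ages, only 12 months lies after enrolment and the programme for every mother now eligible. An earlier age becomes possible only if eligibility is reconciled with the Abstract.

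**Effect on sample size (illustration under assumptions).** The article fixes no sample size. Assume 80% power, two-sided 0.05 and no clustering, so that (1.960 + 0.842)² ≈ 7.849. The 51% is the exclusive breastfeeding figure quoted in the Background for women with gestational diabetes; the comparison rates and the score difference are assumptions.

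- Proportions: n per arm = 7.849 × [p₁(1 − p₁) + p₂(1 − p₂)] / (p₁ − p₂)².
- 51% vs 61%: 7.849 × (0.2499 + 0.2379) / 0.01 ≈ 383.
- 51% vs 71%: 7.849 × (0.2499 + 0.2059) / 0.04 ≈ 89.4, so about 90.
- Score difference of 0.5 SD: 2 × 7.849 / 0.25 ≈ 63.

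A feeding outcome may therefore need clearly more mothers than a score. Allocation by centre would raise all three figures.

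**The case against.** The strongest reply is that this is a condensed article. The full content and scoring of the questionnaire rest on two cited sources that are not at hand, the tool's second name refers to behaviour, and the Abstract promises an assessment after delivery. The questionnaire may carry intention or feeding questions outside the 52 rated items.

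This limits how far the point can go. A reader might infer that the trial cannot answer its third-phase question at all. The documents do not support that: they show only that the instrument as described cannot answer it, and a separate measure would close the gap. The reply does not remove the contradiction, however. The article does not leave the outcome measure to a fuller document. It names the instrument, says that intention and behaviour are measured with it, and then assigns all items elsewhere. The second name does not help, because the items are described as attitudes, norms and perceived control, not feeding practice.

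A reader might also infer a multiplicity problem from five constructs tested at 0.05, or a defect in the absence of a test for a binary feeding outcome. Neither stands as a finding. As described there are three scores rather than five. Labelling a primary outcome and controlling multiplicity are commonly left to an analysis plan, and the third-phase goal already puts behaviour first. The missing binary test only follows from the missing feeding measure.

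**Conclusion.** The contradiction is real and should be resolved before the third phase starts. As described, 0 of 52 items measure intention or behaviour, yet both are claimed for the tool and both are third-phase objectives. The trial could report on attitude, norms and perceived control, but could not support a conclusion on breastfeeding behaviour or intention.

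The item count is certain. The conclusion assumes that the printed breakdown is complete and that no separate measure exists outside the article. It does not depend on sample size, power or significance level.

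**What to change.** In the third-phase objectives and the quantitative Data analysis section:

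1. Delete the claim that the Breastfeeding Drop tool measures intention and behaviour. If the full questionnaire does hold such questions, describe them and correct the item breakdown.
2. Add a maternal-report feeding measure (exclusive, any, stopped) at one fixed infant age after delivery, and compare it between groups as the behaviour outcome.
3. Choose that age so that it falls after enrolment and after the programme for every eligible mother. This requires reconciling the quantitative inclusion criteria, which admit mothers with infants up to 6 months, with the 30–34 weeks in the Abstract.
4. Add a short intention measure before and after the intervention. A baseline measure alone would not serve the stated before/after objective.
5. Keep the three tool domains as secondary outcomes that show mechanism.

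The cost is a few added questions and possibly one brief extra contact, since the article gives no time for its post-delivery assessment. The change may not be free in numbers: the pilot planned under Sample size should size the trial on the feeding outcome, which may need more mothers than a score would. As no sample size is fixed yet, this can still be settled.
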